**Table 1 Tab1:**
[figure not shown]
SPIRIT figure illustrating study events and timings.

*-t*_*1*_ prior to allocation; *t*_*0*_ time zero, at allocation; *t*_*1*_ time 1, after the first ultrasound cannulation; *t*_*2*_ time 2, after each cannulation.

To address the first aim (methodological), which is to assess the feasibility of the proposed design and processes and inform sample size calculations for a larger multi-site study to test the efficacy of the use of POCUS guidance for haemodialysis cannulation, the primary outcome measures are:Participation rates of patients and nurses (implementation)Nurse adherence to and usability of POCUS-guided cannulation in haemodialysis (implementation)Procedural time (implementation), patient perceptions of POCUS-guided cannulation (acceptability)Nurse perceptions of POCUS-guided cannulation (acceptability, implementation, integration)

To address the second aim (clinical), which is to determine whether POCUS-guided needle insertion improves successful cannulation and cannulation accuracy, the outcome measures assessed at each haemodialysis session are:Successful cannulation on first attempt of arterial and venous needlesAccuracy of arterial and venous needle tip placementTotal number of extravasationsPatient pain score

### Design

The study protocol was developed following the SPIRIT (Standard Protocol Items: Recommendations for International Trial) guidelines [16].

A controlled, random order crossover design will be used for this pilot and feasibility study. The study will evaluate two conditions: (1) POCUS-guided cannulation and (2) standard practice of blind cannulation. Each one of up to 20 participant patients will be exposed to each condition implemented by each one of the 10 participant nurses. An independent statistician will produce balanced sequences of conditions and nurses, and a random list to allocate patients to the different sequences at enrolment (each nurse interacting with each patient twice, one using ultrasound and the other using standard blind cannulation). The statistician will be blinded to participant and nurse characteristics. This crossover design (across conditions and nurses) controls for differences between patient characteristics and differences in nurses’ skills, increasing the statistical efficiency, and thus decreasing the overall sample size required for the study [17]. Essentially, each patient within the study acts as his/her own control, thus decreasing the effect of individual factors such as AVF diameter, AVF depth, AVF age, condition of skin, presence of aneurysm or false aneurysm, patient comorbidities, and patient age. In addition, individual nurse factors such as experience with cannulation, ultrasound experience, and self-efficacy will be balanced across all patients.

Quantitative data will be collected at each haemodialysis session to assess whether each cannulation was successful and the location of the needle inside the vessel. At the end of each haemodialysis session, further qualitative data will be collected via structured interviews to elicit patients’ opinions on each cannulation and to identify differences and commonalities in their responses. At the conclusion of the study, nurses will be interviewed using individual or focus groups interviews to collect and analyse their opinions on ultrasound-guided cannulation.

### Setting

The setting for the study is a 16-chair haemodialysis unit in regional Australia. Forty patients receive haemodialysis in the unit each week from Monday to Saturday. The majority of patients undergo haemodialysis three times per week. Twenty registered nurses are employed within the unit on a full- or part-time basis. There are no enrolled nurses or patient care technical staff employed at this site. Data from patients will be collected for 2 days per week (Thursday and Friday) because all potential patients for inclusion attend haemodialysis on these days. Additionally, the patients are expected to be more haemodynamically stable because they have only had 1 day between haemodialysis treatments, as opposed to after the 2-day gap over the weekend when they are more likely to have fluid and electrolyte imbalances. Although a multi-site pilot study would enable an assessment of the feasibility of the study design in different sites, this is an unfunded study that is subject to time constraints. Hence, a pragmatic decision was made to limit the study to a single site.

### Ethical considerations

Ethics approval has been granted from Barwon Health Human Research Ethics Committee (17/112) and Deakin University Research Ethics Committee (2017–367). Registration is approved by the Australian New Zealand Clinical Trials Registry: ACTRN12617001569392 (21/11/2017). Written consent will be obtained from patients and nurses who express interest in participating. Participation is voluntary for all patients and nurses, and they can withdraw at any stage of the study.

### Inclusion and exclusion criteria

*Patients*. The patients included in the study are over the age of 18 years attending the dialysis unit, diagnosed with end-stage renal failure, and receiving haemodialysis three or more times per week via a native AVF will be eligible to participate. The AVF must have been cannulated for routine dialysis treatment for more than 2 months, as the protocol in this dialysis unit is to cannulate all new AVFs with plastic cannulae under either static POCUS assessment or dynamic POCUS guidance for a minimum of 2 weeks and up to 8 weeks, after which patients will change to metal needles (patients new to dialysis start at an acute site within this renal service, not at the study site). Patients must also be using metal needles, as plastic cannulae are generally only used in this unit for new and very difficult cannulations. Patients who cannot give consent or cannot speak English will not be eligible. AVGs are not included in this study as there are no patients with AVG in situ at this dialysis unit and there is only a small percentage used in Australian dialysis units.

*Nurses*. All registered nurses working either full-time or part-time within the unit who have completed the supernumerary haemodialysis training period of 4 weeks will be eligible to participate.

### Target sample size

The target sample size will be 20 patients (based on 30 patients attending the unit with an AVF in situ) and 10 nurses (based on 20 nurses working in the unit). It is estimated that data collection will take place over 12 months. This timeframe is based on a calculation of 10 part-time nursing staff on a rotating roster and takes into account sick and annual leaves and potential patient attrition throughout the study. Nurses will complete both POCUS-guided and blind cannulations on all patients participating in the study in the timeframe.

### Recruitment

All eligible patients and nurses will be invited to participate in the study. The nurse unit manager will give eligible patients a plain language statement detailing the study purpose, procedure, expectations of participants, benefits and risks associated with participation, and the contact details for researchers and Ethic Committee managers. Individuals who express to the nurse unit manager their interest in participating will then be approached by the researcher inperson in the dialysis unit. Information about the study will also be disseminated to eligible nurses in an information session and by email prior to the beginning of the study. Recruitment will continue until the intended sample size is reached.

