Tool	Assessing	Participants	Time period
Structured observational tool	Implementation: participation rates (number of participating patients or nurses related to number of eligible patients or nurses). Overall recruitment, retention, and questionnaire completion rates	Patients Nurses	Throughout the data collection phase
Patient satisfaction survey	Acceptability: patient satisfaction with cannulation technique, use of point-of-care ultrasound	Patients	After each cannulation
Nurse satisfaction survey	Acceptability: nurse satisfaction with cannulation technique and use of point-of-care ultrasound	Nurses	After first cannulation with ultrasound After the half way point of the cannulation data collection
Researcher study notes (diary)	Implementation: protocol adherence by nurses; issues verbalised by nurses, other staff, or patients regarding the study protocol, reasons for drop-out for both patients and nurses	Patients and nurses	Throughout data collection phase
Image assessor measurement survey	Implementation: image assessor’s confidence in accuracy of measurements	Image assessor	Following completion of all needle placement measurements
Structured interview or focus group	Acceptability, demand, implementation, and integration: suitability, usability, barriers and facilitators, sustainability	Nurses	Following completion of the cannulation data collection phase

Once haemodialysis is started, the vascular access nurse expert, using the Terason uSmart 3200 T ultrasound, will take static ultrasound images in both transverse and longitudinal planes, save the images to a portable storage device, and print them for image assessor review.

A third person (image assessor), who is experienced in renal vascular access, will review the images and record data on needle positioning. The image assessor will be blinded to patient, nurse, and condition and will measure (with a ruler) the location of the needle relative to the right and left side (transverse image only) of the vessel and the top and bottom of the vessel (transverse and longitudinal images). The image assessor will complete a short, structured survey at the end of the data collection phase to capture their perceptions about the ease of conducting measurements, the image quality, and their confidence in accuracy of their measurements (see Fig. 1).

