### Data analysis

Patients’ demographic and clinical data and nurses’ demographic and experience data will be reported as means and standard deviations or frequencies and proportions. The overall study feasibility, implementation feasibility, and acceptability will be reported using descriptive statistics. For feasibility, we will report the proportion of patients/nurses eligible for the study, the proportion of patients/nurses enrolled among those eligible, the reasons for declining participation, the proportion of patients/nurses completing the study, and the reasons for completing or not completing the study.

The implementation feasibility will be reported according to patients’ and nurses’ protocol adherence rate, the proportion of time that nurses adhered to the protocol, and the image assessor’s self-reported confidence regarding the accuracy of their measurements (Likert scale). Acceptability will be reported as the proportion of patients expressing satisfaction and the nurse satisfaction survey results related to the cannulation technique and use of point-of-care ultrasound-guided cannulation. Other data related to extravasations and nurse cannulation and ultrasound experience will be summarised using rates and proportions.

Data collected from semi-structured individual and focus groups interviews will be audio-recorded, transcribed verbatim, de-identified, and undergo content and thematic analyses based on a naturalistic inquiry approach.

The potential effect of the POCUS-guided cannulation on the clinical outcomes (miscannulations [0, 1, 2]), location of the needle in the vessel, and duration of the procedure will be estimated using generalised linear mixed models with link and distribution selected based on the type of outcome. The models will include the patient and nurse as random effects, and the condition, period (order in the sequence), and first carry-over effect as fixed effects.

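### Once recruitment reaches its target, the primary participation rate equals target divided by eligible and is only a lower bound on uptake

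*Protocol article*

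**What the plan says.** The list of primary outcome measures for the methodological aim, placed after Table 1, opens with "Participation rates of patients and nurses (implementation". Table 6 defines the measure as "participation rates (number of participating patients or nurses related to number of eligible patients or nurses", and the Data analysis section repeats it as "the proportion of patients/nurses enrolled among those eligible".

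The Recruitment section begins "All eligible patients and nurses will be invited to participate in the study" and ends "Recruitment will continue until the intended sample size is reached".

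The Target sample size section sets both numbers. The nurse figure is half of the staff: "10 nurses (based on 20 nurses working in the unit". The patient figure is two thirds of those with a fistula, and the Design section treats it as an upper limit: "Each one of up to 20 participant patients will be exposed to each condition implemented by each one of the 10 participant nurses".

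**The concern.** The outcome is a ratio whose numerator stops growing at a preset number. Each target is smaller than the pool from which it is drawn. If at least 20 patients or at least 10 nurses agree, enrolment ends there, and anyone else who would have agreed stays in the denominator as a non-participant. In statistical terms, the outcome is censored from above.

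The censoring acts in the scenario the plan hopes for, which is successful recruitment. With 20 eligible nurses, a unit where 10 would take part and a unit where all 20 would take part both report 50%. The Background gives the pilot the task of informing recruitment for a larger multi-site study. A reader who takes the reported rate as an estimate of uptake could therefore understate what other units can achieve.

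**Working it through.** **Inputs.** Patient target 20, pool 30 with an AVF; nurse target 10, pool 20 employed (Target sample size). The rate is enrolled/eligible (Table 6, Data analysis). The article gives no participation percentage and no eligible count, so there is no stated figure to reproduce.

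**Step 1: the ceiling.** With target T and N eligible persons, the largest possible rate is T/N.

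- Patients, N = 30: 20/30 = 66.7%
- Nurses, N = 20: 10/20 = 50.0%

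Both lines assume that everyone in the pool is eligible. The Inclusion and exclusion criteria section narrows both pools: for patients by dialysis frequency, time the AVF has been in use, needle type, capacity to consent and English; for nurses by completed training. Each exclusion lowers N and raises the ceiling. The smaller values of N below are assumptions:

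- Patients: N = 28 gives 20/28 = 71.4%; N = 25 gives 80.0%; N = 22 gives 90.9%; N = 20 gives 100%
- Nurses: N = 18 gives 10/18 = 55.6%; N = 16 gives 62.5%; N = 10 gives 100%

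So, with the stated pools, 67% and 50% are the lowest values the ceilings can take. The ceiling also moves with the eligible count when willingness has not changed.

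**Step 2: how much information is lost.** Suppose each eligible person would agree independently with probability w (an assumption). The number who would agree is X ~ Binomial(N, w). The expected reported rate is E[min(X, T)]/N, and the target fills with probability P(X ≥ T). Taking N = 30 patients and N = 20 nurses:

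| True w | Patients: expected rate | Patients: P(target fills) | Nurses: expected rate | Nurses: P(target fills) |
|---|---|---|---|---|
| 30% | 30.0% | <0.01 | 29.9% | 0.05 |
| 40% | 40.0% | <0.01 | 38.9% | 0.25 |
| 50% | 49.9% | 0.05 | 45.6% | 0.59 |
| 60% | 58.9% | 0.29 | 48.9% | 0.87 |
| 70% | 64.7% | 0.73 | 49.9% | 0.98 |
| 80% | 66.5% | 0.97 | 50.0% | >0.99 |
| 90% | 66.7% | >0.99 | 50.0% | >0.99 |
| 100% | 66.7% | 1 | 50.0% | 1 |

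At low willingness the rate follows w closely. From about 70% upward for patients and 60% upward for nurses it is nearly flat. Patient willingness of 70% and 100% differ by 30 points, but the expected rates differ by only 66.7 − 64.7 = 2.0 points. For nurses at 60% and 100%, a 40-point difference becomes 50.0 − 48.9 = 1.1 points.

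With 25 eligible patients the flattening starts later: expected rates are 69.5%, 76.9% and 79.8% at w = 70%, 80% and 90%.

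**The case against.** The strongest reply is that the measure works where a feasibility study most needs it. If fewer than 20 patients or 10 nurses agree, the cap does not bind and the rate reports uptake correctly. Failure to recruit would be seen. This stands. A reader might infer that the rate measures the target and never willingness, but the plan does not support that: the loss is confined to the case where recruitment has succeeded.

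A reader might also take 67% and 50% as the highest rates that could be reported. That is not supported either. The denominator is eligible persons, whereas 30 and 20 count AVF patients and employed nurses before the eligibility criteria are applied.

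Third, the article plans to report why people declined, and Table 6 also lists overall recruitment. Two units with the same 50% could therefore look different in the decline reasons. This stands in part. Someone who was willing but not needed has not declined, and no listed measure has a place for that person.

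Finally, the rate is reported descriptively, the article ties no progression threshold to it, and nowhere says that the ratio itself will be carried into the multi-site recruitment forecast. This stands, and it lowers the importance of the point. A detailed flow log may well sit in the fuller protocol, but the definition of the outcome is stated in the article, and following it produces the censored rate.

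**Conclusion.** The point holds conditionally. If the target is reached, the primary participation rate equals target/eligible and should be read as a lower bound on uptake. If the target is not reached, the rate tracks uptake. The ceiling is 67% for patients and 50% for nurses when all 30 AVF patients and all 20 nurses are eligible, and higher otherwise. The eligible counts are not given, so the exact ceilings are unknown. The flattening in the table rests on independent binomial agreement and on full eligibility of both pools.

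The change is worth making because it alters what a first-listed primary outcome reports in the scenario the plan aims for. It is not essential to the validity of the study: no stated decision threshold depends on the rate, and it enters no model of the clinical outcomes.

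**What to change.** In Table 6 and in Data analysis, define the participation rate as number agreeing divided by number invited. Since every eligible person is to be invited, this denominator already exists in the plan. Count people who agree after the target is full as agreeing, and list them separately as willing, not enrolled. They will not go on to sign consent, so state which answer counts as agreeing and apply the same rule to everyone.

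Keep enrolled/eligible as a flow count beside the numbers invited, agreeing and declining, and add a sentence that it is a lower bound on uptake once the target is met.

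The cost is a reworded definition in two places and a short log of each invitee's answer, kept up after the target fills. Enrolment, allocation and treatment do not change.

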### Data collection, outcome measures, and procedures

Data collection and management will proceed in accordance with the SPIRIT guidelines as represented in the SPIRIT figure in Table 1.

Baseline demographic data will be collected via a survey (Table 2).

**Table 2 Tab2:** Baseline data collected at enrolment

Nurses	Patients
Age	Age
Sex	Sex
Dominant hand	Type of AVF
Years of experience in dialysis	Comorbidities
Years of experience with cannulation	Other relevant medical history
Years of experience with ultrasound	Time on haemodialysis
Employment status (full- or part-time)	Frequency of haemodialysis
Completed level of education	Date of AVF creation and first cannulation
Completion of formal or informal ultrasound training	
Frequency of use of ultrasound use to assess AVFs	
Frequency of use of ultrasound to guide cannulation	
Circumstance that prompt to use the ultrasound for guidance	

Nurse participants working at the study site undertake ultrasound competency training on employment and are encouraged to regularly use static POCUS assessment prior to cannulation. The competency training with a vascular access expert involves one training session using ultrasound guidance on training models (namely chicken fillets filled with water balloons).

The aim is for two nurse participants on each morning shift and two nurse participants on each afternoon shift to cannulate two patient participants each during the study. This schedule will capture eight patients per day, 16 patients per week. The patient and nurse participants are each assigned a number (1, 2, 3, etc.) by the researcher based on recruitment order. A statistician, who only knows the total number of patient and nurse participants, will arrange them into dyads via Excel spreadsheet and randomly assign each dyad an allocated condition (POCUS or blind) to be undertaken at first meeting of that dyad (Table 3). At the next meeting of the dyad, the opposite condition would apply (Table 4). Due to the time periods between treatment cannulations and the use of the best practice rope ladder cannulation technique practiced by staff in the unit, evidence of needle placement following use of ultrasound in one session is not anticipated to influence the blind cannulation needle placement in the next session. It is estimated that data collection will take approximately 12 months depending on staff and patient availability.

**Table 3 Tab3:** Example of patient and nurse allocation to condition

	Nurse 1		Nurse 2		Nurse 3		Nurse 4	
	Dyad	First cond	Dyad	First cond	Dyad	First cond	Dyad	First cond
Patient 1	1	Blind	11	POCUS	21	Blind	31	Blind
Patient 2	2	Blind	12	Blind	22	POCUS	32	POCUS
Patient 3	3	Blind	13	POCUS	23	POCUS	33	POCUS
Patient 4	4	POCUS	14	POCUS	24	Blind	34	Blind
Patient 5	5	Blind	15	Blind	25	POCUS	35	POCUS
Patient 6	6	POCUS	16	POCUS	26	Blind	36	POCUS
Patient 7	7	POCUS	17	POCUS	27	POCUS	37	Blind
Patient 8	8	POCUS	18	Blind	28	Blind	38	Blind
Patient 9	9	POCUS	19	Blind	29	Blind	39	POCUS
Patient 10	10	Blind	20	Blind	30	POCUS	40	Blind

**Table 4 Tab4:** Example of patient and nurse condition and data collection sheet

		Nurse 1			Nurse 2	
Patient	Dyad	First meeting (condition from randomisation table)	Second meeting (opposite condition)	Dyad	First meeting (condition from randomisation table)	Second meeting (opposite condition)
1	1	Blind	POCUS	11	POCUS	Blind
		20/4/18	6/6/18		4/4/18	11/4/18
2	2	Blind	POCUS	12	Blind	POCUS
		5/10/18	17/12/18		13/7/18	4/8/18

Specific data collected at each haemodialysis session in relation to the nurse cannulator, patient, and dialysis machine are outlined in Table 5. The researcher will observe every cannulation in each treatment session and record the characteristics listed in Table 5 for both the venous and the arterial cannulation. A cannulation will be defined as successful (0) if the needle for haemodialysis is inserted without miscannulation or manipulation, or unsuccessful (1) if the needle extravasates the vessel or blood cannot be accessed from the needle. The number of miscannulations in a session will then take values 0, 1, or 2. For example, a nurse cannulates with the first (arterial) needle and extravasates the vessel, the needle is removed, and pressure applied to the site. This is recorded as ‘1’. In a second attempt, the arterial needle is appropriately placed in the vessel, i.e. it is successful, so this is recorded as ‘0’. The venous needle is also inserted successfully and recorded as ‘0’. The total number of miscannulations for this patient would be ‘1’. In consultation with management of the dialysis unit, the maximum allowable number of blind cannulations for a patient treatment is set at four, a maximum of two cannulations per site. For example, if a nurse miscannulates twice on the arterial point using the standard practice of blind cannulation, they would then use POCUS guidance to cannulate the third time. This information will be recorded by the researcher observing the process. If the cannulator deems POCUS guidance necessary after one miscannulation, this is acceptable and will be documented as above.

**Table 5 Tab5:** Data collected during the study

Nurses	Patients	Dialysis machine
Sitting or standing to cannulate	Patient arm position	Pump speed (Qb)
Use of gloves (sterile or non-sterile)	Patient-reported pain score (scales 1–10) each needle	Venous and arterial line pressures
Ultrasound probe held longitudinal or transverse	Patient-reported perception of the cannulation experience (scales 1–10)	Any initial pressure alarms
Cannulate in one or two motions	Patient additional comments re-cannulation or ultrasound process	
Needle manipulation once inserted	Ultrasound images in both transverse and longitudinal planes	
Time from tourniquet application until machine started		
Miscannulations (needle removed and re-sited)		
Nurse-reported perceptions of the use of ultrasound

**Table 6 Tab6:** Feasibility assessments

Tool	Assessing	Participants	Time period
Structured observational tool	Implementation: participation rates (number of participating patients or nurses related to number of eligible patients or nurses). Overall recruitment, retention, and questionnaire completion rates	Patients Nurses	Throughout the data collection phase
Patient satisfaction survey	Acceptability: patient satisfaction with cannulation technique, use of point-of-care ultrasound	Patients	After each cannulation
Nurse satisfaction survey	Acceptability: nurse satisfaction with cannulation technique and use of point-of-care ultrasound	Nurses	After first cannulation with ultrasound After the half way point of the cannulation data collection
Researcher study notes (diary)	Implementation: protocol adherence by nurses; issues verbalised by nurses, other staff, or patients regarding the study protocol, reasons for drop-out for both patients and nurses	Patients and nurses	Throughout data collection phase
Image assessor measurement survey	Implementation: image assessor’s confidence in accuracy of measurements	Image assessor	Following completion of all needle placement measurements
Structured interview or focus group	Acceptability, demand, implementation, and integration: suitability, usability, barriers and facilitators, sustainability	Nurses	Following completion of the cannulation data collection phase

Once haemodialysis is started, the vascular access nurse expert, using the Terason uSmart 3200 T ultrasound, will take static ultrasound images in both transverse and longitudinal planes, save the images to a portable storage device, and print them for image assessor review.

A third person (image assessor), who is experienced in renal vascular access, will review the images and record data on needle positioning. The image assessor will be blinded to patient, nurse, and condition and will measure (with a ruler) the location of the needle relative to the right and left side (transverse image only) of the vessel and the top and bottom of the vessel (transverse and longitudinal images). The image assessor will complete a short, structured survey at the end of the data collection phase to capture their perceptions about the ease of conducting measurements, the image quality, and their confidence in accuracy of their measurements (see Fig. 1).

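### The 0–2 range for miscannulations per session does not fit the protocol's own attempt-level scoring, and the modelled outcome is not tied to the declared first-attempt success

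*Protocol article*

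**What the plan says.** All references are to the protocol article.

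- **Declared outcome.** The Abstract and the clinical outcome list under Aims name cannulation success at the first attempt; the list under Aims applies it to the arterial and the venous needle.
- **Definitions.** Under Aims, a success must be free of both miscannulation and manipulation. A miscannulation is a needle that has to be reinserted or replaced. Manipulation is not part of that second definition.
- **Scoring.** Data collection, outcome measures, and procedures repeats the definition of success (code 0) and codes a cannulation "unsuccessful (1) if the needle extravasates the vessel or blood cannot be accessed from the needle". It then says: "The number of miscannulations in a session will then take values 0, 1, or 2".
- **Worked example.** After a failed first arterial attempt, which scores 1, the text reads: "In a second attempt, the arterial needle is appropriately placed in the vessel, i.e. it is successful, so this is recorded as ‘0". A 0 is likewise given on the venous side, and "The total number of miscannulations for this patient would be ‘1".
- **Attempt limit.** In the same section, "the maximum allowable number of blind cannulations for a patient treatment is set at four, a maximum of two cannulations per site". It foresees a double miss at one needle: "if a nurse miscannulates twice on the arterial point using the standard practice of blind cannulation, they would then use POCUS guidance". An earlier change of technique is also permitted: "If the cannulator deems POCUS guidance necessary after one miscannulation, this is acceptable".
- **Analysis.** Data analysis lists the "clinical outcomes (miscannulations [0, 1, 2"] among the mixed-model outcomes, with needle location and procedure duration. First-attempt success is not named there.

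**The concern.** The protocol gives a range for its session score that its own counting rule can exceed. If every failed attempt counts, sessions with 3 or 4 misses have no valid code. If only first attempts count, the range is right but the rule is nowhere written down. Two people working from the same observation sheets could build different outcome variables.

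The link to the declared outcome is also incomplete. The modelled variable is miscannulations, whereas the declared one is first-attempt success. Manipulation defeats success but is not a miscannulation, so one is not simply the complement of the other.

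At stake is the clinical estimate and the event rate this pilot could pass on to the multi-site sample size. Under attempt-level counting, the score also depends on how many retries were made and when the nurse changed technique. A first-attempt result does not.

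**Working it through.** **Step 1: can the stated range be reproduced?** There are two needles per session and at most two blind attempts per site, so each needle has 0, 1 or 2 failed blind attempts.

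- Counting every failed blind attempt gives possible totals 0, 1, 2, 3, 4. The maximum is 2 sites × 2 = 4. The stated range is not reproduced.
- Counting needles whose first attempt failed gives 0, 1, 2. The stated range is reproduced.
- The worked example gives 1 + 0 + 0 = 1 on the first rule and one needle on the second, so it does not separate them.

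A failed ultrasound attempt after a switch would add to the first count, and no attempt limit is stated for ultrasound sessions.

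**Step 2: where do the two counts differ?** Only when one needle is missed twice:

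| Misses (one needle, other needle) | All failed attempts | Needles failing first time |
|---|---|---|
| 1, 1 | 2 | 2 |
| 2, 0 | 2 | 1 |
| 2, 1 | 3 | 2 |
| 2, 2 | 4 | 2 |

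An attempt total of 2 therefore cannot be turned back into a first-attempt result.

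**Step 3: how often?** The protocol gives no failure probability. Assume independent attempts, the same q at each, and no switch to ultrasound after a single miss. Per needle, P(0 misses) = 1 − q, P(1) = q(1 − q), P(2) = q².

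- P(counts differ) = 1 − (1 − q²)²
- P(total above 2) = 2·q²·q(1 − q) + q⁴ = 2q³ − q⁴
- Mean attempt count = 2(q + q²); mean first-attempt failures = 2q

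Expected numbers use 20 patients × 10 nurses = 200 blind sessions (Design), if all are completed.

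| q | Counts differ | of 200 | Total above 2 | of 200 | Mean, attempts | Mean, first attempt |
|---|---|---|---|---|---|---|
| 0.03 | 0.18% | 0.4 | 0.005% | 0.01 | 0.0618 | 0.060 |
| 0.10 | 1.99% | 4.0 | 0.19% | 0.4 | 0.22 | 0.20 |
| 0.30 | 17.19% | 34.4 | 4.59% | 9.2 | 0.78 | 0.60 |

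**Step 4: manipulation.** A needle that is manipulated, does not extravasate and yields blood is not a 0, because manipulation rules out success. It is not a 1 either, because neither failure condition is met. This gap remains under both counting rules. Its size cannot be computed, as no manipulation rate is given.

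**The case against.** The best defence is that a needle-level count was meant all along. The section has the researcher record both the venous and the arterial cannulation, scores each 0 or 1, and says the session count then runs from 0 to 2. That follows naturally from two needles with one binary score each, and the worked example agrees. Read this way, and leaving manipulation aside, the score is 2 minus the number of first-attempt successes, which is the declared outcome. This stands as a possible reading. Against it, the section scores the second arterial attempt separately, speaks of miscannulating twice at one point, and nowhere limits the count to first attempts.

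A reader might therefore infer that the mixed model answers a different question from the declared one. The documents do not establish that, because the needle-level reading remains open.

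A reader might also be struck that, among blind sessions with an attempt total of 2, the share with only one first-attempt failure is 2/(3 − q): 67%, 69% and 74% at q = 0.03, 0.10 and 0.30. The algebra is right, but the figure is conditional on a total of 2, which occurs in only 0.26%, 2.6% and 17% of blind sessions. It does not measure the overall effect.

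Low q is plausible. Background reports 5 to 25 miscannulations a month in a 16-chair unit. Assume this is the study unit, with 30 fistula patients, three sessions a week, 4.33 weeks a month and two needles: 30 × 3 × 4.33 × 2 ≈ 780 needles, or roughly 0.6% to 3.2%. Clustering of misses in difficult patients would raise the disagreement above the independence figures.

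Finally, the raw observations allow either variable to be derived, the primary measures for the methodological aim concern feasibility, and the Discussion disclaims conclusions on effectiveness. These points limit the seriousness but do not remove the inconsistency.

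**Conclusion.** The point holds as an inconsistency in the outcome definition. The 0–2 range conflicts with attempt-level scoring under the two-per-site blind limit, which allows 0–4. It fits only a first-attempt count that the protocol does not define. The mixed-model sentence does not name the declared outcome, and the manipulated-but-working needle has no code under either reading.

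The numerical consequence for the counting unit is small at low failure rates and appreciable at high ones: about 0.2%, 2% and 17% of blind sessions at q = 0.03, 0.10 and 0.30. These figures rest on independent attempts, equal q and no early switch, none of which the documents confirm. The protocol does not say which event rate will feed the multi-site sample size, so an error there is a risk and not a demonstrated result. The case for changing the text rests on the contradiction and the incomplete mapping more than on the expected numerical shift. The open choice of link and distribution is not part of the point.

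**What to change.** 1. Define the analysed clinical outcome as a binary first-attempt result for each needle, arterial and venous. Code a manipulated needle explicitly as not successful, in line with the definition under Aims.
2. Name that outcome in Data analysis. Analyse it by allocated condition in a mixed model with patient and nurse random effects, either as Bernoulli per needle or as binomial out of 2 per session.
3. Report total miscannulations per session separately as a count, and remove the 0–2 range from that count in both Data collection, outcome measures, and procedures and Data analysis. State whether misses after a change of technique are included.
4. Reconcile Aims, the clinical outcome list, the scoring paragraph and Data analysis on the counting unit and on manipulation.

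The cost is wording only. The researcher observes every cannulation, and Table 5 already records both miscannulation and manipulation. No attempt limit or other clinical rule needs to change.
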